**STUDY COMPONENTS**

The study is divided in three components

1. **Study A: Comparison of the immunogenicity of Rotarix® vaccine when administered at 6 and 10 weeks of age, 10 and 14 weeks of age, and 6, 10 and 14 weeks of age.**
2. **Study B: Impact of withholding breastfeeding around the time of Rotarix® vaccination on the immunogenicity of Rotarix® vaccine.**
3. **Study C: To evaluate baseline seroconversion rate for rotavirus among children in the first 18 weeks of life.**

The specific design elements of each of these three studies are described separately.

1. **research design and methods**

**Study A: Comparison of the immunogenicity of Rotarix® vaccine when administered at 6 and 10 weeks of age, 10 and 14 weeks of age, and 6, 10 and 14 weeks of age.**

- 1. **Study Site**

The study will be conducted at one site in an urban- squatter settlement area, Ali Akber Shah Goth (AG) in Karachi where the Aga Khan University’s Department of Paediatrics and Child Health has demographic surveillance in place, including pregnancy and newborn surveillance. The annual birth cohort in the area is approximately 1600 infants. The site is about 30 minutes driving distance from the Aga Khan University Medical College and Hospital campus. A GIS map of the site is available. The Department will provide EPI immunizations at this location.

[figure not shown]

- 1. **Study Design**

This study will compare the immunogenicity of Rotarix® vaccine when administered in three different schedules:

**Arm 1:** will receive the routine EPI vaccines according to the usual schedule in Pakistan (6, 10 and 14 weeks of age) and the rotavirus vaccine at 6 and 10 weeks of age

**Arm 2:** will receive the routine EPI vaccines according to the usual schedule in Pakistan (6, 10 and 14 weeks of age) and the rotavirus vaccine at 10, and 14 weeks of age

**Arm 3:** will receive the routine EPI vaccines according to the usual schedule in Pakistan (6, 10 and 14 weeks of age) and the rotavirus vaccine at 6, 10, and 14 weeks of age

- 1. **Sample Size Calculations**

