**Visit at 14 weeks**

- EPI vaccination
- 2^nd^ dose Rota virus vaccination
- sample on day’s 3 and 7 after vaccination

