**Visit at 18 weeks**

- Blood draw
  1. **Enrollment Time Period**

Enrolment will be completed over a period of one year so that all the seasons are covered. The rotavirus infections in Karachi are seasonal, with peaks in both summer and winter months which can influence baseline seroconversion. Refer to section 4.5

- 1. **Enrollment Schedule**

| ***Treatment Group*** | ***Number of Subjects*** | **Youngest (Y): 6wk, 0dy**  **Oldest(O): 7wk, 6dy** | **Y: 10wk, 0dy**  **O: 12wk, 6dy** | **Y: 14wk, 0dy**  **O: 17wk 6dy** |
| --- | --- | --- | --- | --- |
| Arm 1 | 200 | Standard EPI + Rotarix® | Standard EPI + Rotarix® | Standard EPI |
| Arm 2 | 200 | Standard EPI | Standard EPI + Rotarix® | Standard EPI + Rotarix® |
| Arm 3 | 200 | Standard EPI + Rotarix® | Standard EPI + Rotarix® | Standard EPI + Rotarix® |

*Standard EPI in Pakistan is OPV plus BCG at birth; DPT-Hep-B-Hib and OPV at 6, 10, and 14 weeks, and measles at 9 months and second year of life

- 1. **Sampling Collection and Handling**

3 ml of blood sample will be obtained by a trained health worker according to WHO standard procedures. Blood draws will be done at 6, 14 and 18 weeks of age. Blood samples from this study will be used only for rotavirus IgA and neutralizing antibody assay testing. Samples will be stored with a unique identification number specific for the study child.

- 1. **Lab Assay**

| ***6wks*** | ***10wks*** | ***14wks*** | ***18wks*** |
| --- | --- | --- | --- |
| **All arms:**  Rotavirus IgA (Serum)  Rotavirus Neutralizing Antibody (Serum) |  | **Arm 1 only**  Rotavirus IgA (Serum) | **All Arms**  Rotavirus IgA (Serum) |
|  |  |  |  |
|  |  |  |  |

- 1. **Laboratory Training for Rotavirus antibody assays**

We will make arrangements with the laboratory of [name] lab in Cincinnati, OH, USA to train one senior laboratory technician from our laboratory in performing rotavirus IgA. Since rotavirus neutralizing antibody assays are complicated and the number of samples that need to be tested for neutralizing assay is small, samples will be shipped to [name] lab in Cincinnati, OH for testing of neutralizing antibodies.

- 1. **Data Entry, Cleaning and Management**

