Seropositivity will be defined as an anti-rotavirus IgA concentration ≥20 U/ml. Seroconversion will be defined as the detection of anti-rotavirus IgA concentration ≥ 20 U/ml in infants seronegative for anti-RV IgA at age 6 weeks before vaccination. The primary analyses will be performed on the according to protocol (ATP) cohort. Rotavirus IgA seroconversion rate (proportion of infants who have rotavirus IgA antibodies in serum sample) by age 18 weeks will be determined for infants in each arm who were rotavirus IgA –negative at 6 weeks of age. The primary endpoint will be the comparison of the rotavirus IgA seroconversion rate at age 18 weeks in arm 3, compared to the greatest IgA seroconversion rate for arm 1 (either the result from the 14 week samples or the 18 week samples). This latter aspect is included in order to provide the most relevant comparison between arms 1, 2 and 3 because both times since last dose of rotavirus vaccine and age at last blood draw can affect seroconversion estimates. Seroconversion rates will be compared between arm 1 and arm 3 using a Chi-square test. Confidence intervals (95%) for the differences in seroconversion rates will also be calculated. Rotavirus IgA GMC (geometric mean concentration) will be calculated and compared between the arms using a t-test. As described above for seroconversion, this would be at age 18 weeks for arms 1 and 3, and the highest result from the 14- and 18 week sample for arm 2.

- 1. **Role of Maternally derived Rotavirus Neutralizing antibodies in the immunogenicity of Rotavirus vaccine:**

The distribution of the level of maternally-derived rotavirus antibodies in the 6 week serum samples (among those infants who were rotavirus IgA negative at age 6 weeks and completed the study ATP) will be examined. The independent effect of the level of maternally-derived neutralizing antibody level on the rate of rotavirus IgA seroconversion by age 18 weeks will be assessed using logistic regression. Vaccine schedules will be included {(Arm 1 vs. Arms 3(primary) and Arm 1 vs. Arm2 (secondary)} as an independent variable and effect modification by neutralizing antibody level will be examined. Exploratory analyses will be performed for correlation between maternally-derived neutralizing antibody level and rotavirus IgA level at age 18 weeks among the two vaccine schedule categories

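### Study A's GMC rule gives the 14/18-week choice to arm 2 instead of arm 1, so it contradicts the seroconversion rule it cites and calls for an arm 2 result that is not scheduled

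*Protocol*

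**What the plan says.** The section on analysis of immunogenicity for Study A (3.18) holds two timing rules.

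- **Seroconversion, the primary endpoint.** Arm 3 at 18 weeks is "compared to the greatest IgA seroconversion rate for arm 1 (either the result from the 14 week samples or the 18 week samples". The reason given is that "both times since last dose of rotavirus vaccine and age at last blood draw can affect seroconversion estimates".
- **GMC.** The arms are compared by t-test, with this timing: "As described above for seroconversion, this would be at age 18 weeks for arms 1 and 3". The sentence then gives the choice between the two ages to arm 2. In full, the timing is "at age 18 weeks for arms 1 and 3, and the highest result from the 14- and 18 week sample for arm 2".

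Four other places in the protocol bear on this.

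- **Study design.** Arm 2 receives "the rotavirus vaccine at 10, and 14 weeks of age". Arm 1 is vaccinated at 6 and 10 weeks, and arm 3 at 6, 10 and 14 weeks.
- **Lab assay table.** Serum IgA is tested at 6 and 18 weeks in all arms, and at 14 weeks in arm 1 only.
- **Vaccination and blood draw schedule.** Blood is taken just before vaccination. Of the three 14-week visit boxes, only the one without a Rotarix dose (arm 1) lists a blood draw. The box with the second dose (arm 2) lists only a "sample on day’s 3 and 7 after vaccination", with no specimen type.
- **Sampling collection and handling (3.13).** "Blood draws will be done at 6, 14 and 18 weeks of age", with no arm named.

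**The concern.** The GMC sentence claims to repeat the seroconversion rule but applies it to a different arm. Two things follow if it is read literally.

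First, the arm 2 term needs a 14-week IgA result that the assay table does not plan. Such a sample would in any case be taken before arm 2's second dose.

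Second, arm 1's GMC is tied to 18 weeks and its scheduled 14-week result is dropped, while its seroconversion rate may use that result. The two immunogenicity readouts for one arm could then differ because of timing alone. That is the influence the protocol says it wants to handle.

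An analyst would have to depart from the text to run the arm 2 comparisons. The text does not say how, and the choice could be made after the titres are known.

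**Working it through.** **1. The plan's own figure.** The only stated figure near this analysis is the 191 per arm in Sample Size Calculations, built on seroconversion of 35% in arm 1 against 52.5% in arms 2 and 3, power 0.85, two-sided alpha 0.05, 20% dropout and 5% seropositive at 6 weeks.

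n = [1.960·√(2·p̄·(1−p̄)) + 1.036·√(p₁(1−p₁) + p₂(1−p₂))]² / (p₁−p₂)², with p̄ = (0.35 + 0.525)/2 = 0.4375

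- First term: 1.960 × √0.4922 = 1.375
- Second term: 1.036 × √(0.2275 + 0.2494) = 0.716
- n = (2.091)² / 0.0306 = 142.7, rounded up to 143
- 143 / (1 − 0.20 − 0.05) = 190.7, rounded up to 191

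The figure reproduces. It uses only seroconversion rates, so the GMC rule has no bearing on it.

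**2. What each rule needs against what is scheduled.**

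| | Arm 1 | Arm 2 | Arm 3 |
|---|---|---|---|
| Rotarix doses (weeks) | 6, 10 | 10, 14 | 6, 10, 14 |
| Doses received before a 14-week draw | 2 of 2 | 1 of 2 | 2 of 3 |
| 14-week IgA scheduled | yes | no | no |
| 18-week IgA scheduled | yes | yes | yes |
| Seroconversion rule for the primary comparison | greater of 14 and 18 weeks | not in this comparison | 18 weeks |
| GMC rule as written | 18 weeks | highest of 14 and 18 weeks | 18 weeks |
| GMC rule if arms 1 and 2 are exchanged | higher of 14 and 18 weeks | 18 weeks | 18 weeks |

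As written, one of the two components of the arm 2 term is unscheduled for all 200 planned infants. With the two labels exchanged, every required result is scheduled.

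**3. Nominal time from last dose to sample.**

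- Arm 1 at 14 weeks: 14 − 10 = 4 weeks
- Arm 1 at 18 weeks: 18 − 10 = 8 weeks
- Arms 2 and 3 at 18 weeks: 18 − 14 = 4 weeks

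Only arm 1 has a 14-week sample taken after its full course, and only there does that sample match the 4-week interval of the other arms. The stated reason for having two timepoints therefore fits arm 1 and not arm 2.

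**4. Does it matter how the highest result is chosen?** The text does not say whether the choice is made per infant or per arm. This was checked under assumptions that are not in the protocol: log-normal titres, equal true means at both ages and in both arms, and within-infant correlation ρ of 0.5 to 0.9. The number evaluable was taken as 200 × 0.80 × 0.95 = 152 per arm. For a per-infant maximum the expected upward shift in mean log titre is √((1−ρ)/π) SD, and for an arm-level choice it is that value divided by √152. A simulation of 20,000 trials at each ρ gave:

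| ρ | Per-infant shift (SD) | t-test rejects with no true difference | Arm-level shift (SD) | t-test rejects with no true difference |
|---|---|---|---|---|
| 0.5 | 0.40 | 95% | 0.03 | 5% |
| 0.8 | 0.25 | 61% | 0.02 | 5% |
| 0.9 | 0.18 | 34% | 0.01 | 5% |

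The arm-level choice does almost no harm in this setting. A per-infant maximum would distort the comparison badly.

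**The case against.** The strongest reply is that this is a slip of two arm labels in a supporting analysis. The same sentence points back to the seroconversion rule, and the assay table shows which arm has the 14-week result, so a careful analyst would recover the intent. GMC is not the primary endpoint, and Primary Aim 1 and its schedule-comparison secondary aim name only seroconversion. This stands as a limit on importance. It does not remove the error: the protocol fixes a rule that cannot be followed for arm 2, and the correction changes which result feeds arm 1's GMC.

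The protocol also plans seroconversion by 18 weeks in every arm, so an 18-week GMC would have an 18-week counterpart. That softens the mismatch, but the primary comparison may still use arm 1 at 14 weeks.

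Three stronger readings are tempting, and the protocol does not support them.

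- *The whole GMC comparison cannot be run.* Only the arm 2 term and the comparisons using it are affected. Arm 1 against arm 3 at 18 weeks can be computed from scheduled assays.
- *The rule biases the GMC upward.* That requires a per-infant maximum, which is not stated. The rule it refers back to works at arm level, where the shift is negligible under the assumptions shown. What remains is an ambiguity to close.
- *Section 3.13 orders a 14-week draw in arms 2 and 3, up to 400 samples with no assay.* This takes the broadest reading of a general list of sampling ages, which the visit boxes and assay table then narrow. It is loose wording.

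**Conclusion.** The inconsistency is real, and the rule is wrong as written. The GMC sentence contradicts the seroconversion rule it invokes. Its arm 2 term has no scheduled 14-week result, and arm 1's GMC would be read nominally 8 weeks after the last dose against 4 weeks in arm 3, with the scheduled 4-week result ignored. Exchanged arm labels are the likeliest cause, an inference from the sentence's own back-reference and the assay table.

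The effect is confined to a supporting analysis. The primary seroconversion comparison and the 191 per arm are untouched. The intervals are nominal, since the protocol allows visit windows of several weeks. The conclusion rests on comparing the protocol's sections. The simulation supports only the advice to say how the higher result is chosen.

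**What to change.** In section 3.18, reword the GMC rule before any titres are seen:

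- Arms 2 and 3: GMC at 18 weeks.
- Arm 1: the same 14/18-week rule as its seroconversion endpoint, stated as the higher of the two arm-level GMCs and not as a per-infant maximum.
- Report arm 1's GMC at both 14 and 18 weeks, so that readers can see the effect of time since last dose.

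If the seroconversion endpoint is ever changed to one fixed age, the GMC rule should use that same age. Setting 18 weeks for all arms for GMC alone would leave arm 1 with different timing for its two readouts and would keep the 8- against 4-week gap.

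In section 3.13, reword the general sentence so that the 14-week draw in Study A matches the visit schema and assay table (arm 1 only). Studies B and C refer back to this section for sampling, so the reworded sentence should leave their own schedules in force.

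The cost is wording only. No new samples, assays or infants are needed.

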**Study B: Impact of withholding breastfeeding around the time of Rotarix® vaccination on the immunogenicity of Rotarix® vaccine.**

- 1. **
[figure not shown]
Study Site**

The study will be conducted at one site in an urban- squatter settlement area, Ibrahim Haidry in Karachi where the Aga Khan University’s Department of Paediatrics and Child Health has demographic surveillance in place, including pregnancy and newborn surveillance. The annual birth cohort in the area is approximately 1800 infants. The site is about 30 minutes driving distance from the Aga Khan University Medical College and Hospital campus. A GIS map of the site is available. The Department will provide EPI immunizations at this location.

- 1. **Study Design**

This study will compare the immunogenicity of Rotarix ® vaccine in relation to the timing of breast feeding. The two arms of the study will receive the EPI vaccines according to the usual schedule in Pakistan at ages 6, 10 and 14 weeks and Rotarix® vaccine at 6, 10, and 14 weeks of age. In arm 1, mothers would be asked to breast feed immediately before administration of the Rotarix dose. In arm 2, mothers would be asked to withhold breast feeding for one hour before and one hour after each Rotarix®dose.

Infants potentially eligible for the study will be identified by the CHWs during their routine household surveillance, and will be brought to the PHC at 4 weeks of age or at the time of first contact with the baby. In the PHC, infants will undergo history and physical examination by the study medical officer to determine eligibility. Study procedures will be explained to the mothers, including the need to withhold breastfeeding or to breastfeed at time of the vaccine doses, depending on the study arm. Consent will be asked from the parents of infants who are eligible. After obtaining consent, infants will be randomized into the breast feeding with holding or immediate breastfeeding arms.

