Mothers who earlier provided consent and were randomized to the immediate breastfeeding group will be picked up at their home approximately 1 hour before the expected immunization time and instructed not to breastfeed until the indicated time. They will be taken to the clinic, infant blood sample will be obtained, routine EPI immunization will be given and mother will be asked to breastfeed the baby for at least 20 minutes. CHW staff will observe the breastfeeding. The Rotarix vaccine will be given, and then baby will be observed for 20 minutes to document if any vomiting occurred.

Mothers who earlier provided consent and were randomized to the withholding breastfeeding group will be picked up at their home approximately 1 hour before the expected immunization time and instructed not to breastfeed until the indicated time. They will be taken to the clinic, infant blood sample will be obtained, routine EPI immunization will be given, Rotarix vaccine will be given, and then mother will be asked to not breastfeed for one hour after the dose. CHW staff will observe the mother and infant during this period and document withholding of breastfeeding and to document if any vomiting occurred. After the 1 hour period, the mother will be able to breastfeed the infant if desired.

On the day of each vaccine visit, the mother will be asked to express 10 ml of breast milk into a study container while the CHW is present in the home to assist as needed or in the clinic and to refrigerate the sample as soon as it is expressed.

At age 6, 14 and 18 weeks, in breast feeding withholding arm 1 ml of oral fluid (OF) will be taken from infants in order to determine the correlation of IgA in OF and serum. Arm 1 provides an ideal setting to assess the value of non-invasive OF assays for rotavirus immune response, avoiding the potential contamination from breast milk.

- 1. **Sample Size consideration:**

Target enrollment would be 400 infants (200 each in each group) to be able to detect a difference in seroconversion rate of at least 17.5% between the withholding breastfeeding group and the immediate breastfeeding group, if such a difference truly exists.

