**Withholding Breastfeeding Arm (Arm 2)**

n= 200

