**Immediate Breastfeeding Arm (Arm 1)**

n=200

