**Visit at 14 weeks**

- Breast milk sample obtained from mother
- 3^rd^ dose Rota virus vaccination
- Blood and oral fluid samples obtained from infant
- EPI vaccines given
- One hour withholding of breast feed before and after vaccination

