**Visit at 18 weeks**

- Blood and oral fluid samples obtained from infant
  1. **Lab Assay**

| **Youngest (Y): 6wk, 0dy**  **Oldest(O): 7wk, 6dy** | **Y: 10wk, 0dy**  **O: 12wk, 6dy** | **Y: 14wk, 0dy**  **O: 17wk 6dy** | **Y: 18wk, 0dy**  **O: 22wk, 6dy** |
| --- | --- | --- | --- |
| ***Infant serum*** |  | ***Infant serum*** | ***Infant serum*** |
| Rotavirus IgA  Neutralizing Antibodies |  | Rotavirus IgA | Rotavirus IgA |
| ***Oral fluid(withholding group only )*** |  | ***Oral fluid(withholding group only )*** | ***Oral fluid(withholding group only )*** |
| Rotavirus IgA |  | Rotavirus IgA | Rotavirus IgA |
| ***Breast milk sample*** | ***Breast milk sample*** | ***Breast Milk sample*** |  |
| Rotavirus IgA  Rotavirus Neutralizing Activity | Rotavirus IgA  Rotavirus Neutralizing Activity | Rotavirus IgA  Rotavirus Neutralizing Activity |  |

- 1. **Sampling Collection and Handling**

Same as section 3.13

- 1. **Laboratory Training and testing for rotavirus antibody assays**

Serum rotavirus IgA and rotavirus neutralizing antibody testing will be done as described in section 3.15. Assessment of rotavirus antibody and rotavirus neutralizing activity in breast milk, and rotavirus antibody in oral fluid will be done at CDC- [name] lab, who is the pioneer of this assay.

- 1. **Data Entry, Cleaning and Management**

Same as section 3.16

- 1. **Data Analysis of Demographics**

Same as section 3.16

- 1. **Analysis of immunogenicity**

Seropositivity will be defined as an anti-rotavirus IgA concentration ≥20 U/ml. Seroconversion will be defined as the detection of anti-rotavirus IgA concentration ≥ 20 U/ml in infants seronegative for anti-RV IgA at age 6 weeks before vaccination. The primary analyses will be performed on the according to protocol (ATP) cohort. The primary endpoint will be the comparison of the rotavirus IgA seroconversion rate at age 18 weeks between the immediate breastfeeding and the withholding breastfeeding groups, using a Chi-square test. Confidence intervals (95%) for the difference in seroconversion rates will also be calculated. Rotavirus IgA GMC (geometric mean concentration) at age 18 weeks will be calculated and compared between the arms using a t-test. Similar analyses will be performed comparing the seroconversion rate at age 14 weeks between the two arms.

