The correlation between serum and OF IgA will be determined (1) by the concordance in detecting seroconversion, as defined above, at 14 and 18 weeks and (2) the correlation between antibody titers in OF and serum at age 6,14 and 18weeks. For this analysis a cutoff will not be used. Instead, the simple correlation (represented by the R-squared value) will be calculated between anti-rotavirus IgA titer in serum compared with anti-rotavirus IgA titer in oral fluid. This will give the best indication of how well oral fluid antibody represents antibody in serum.

- 1. **Role of Rotavirus Neutralizing activity in Breast Milk on the immunogenicity of Rotavirus vaccine:**

The distribution of the level of rotavirus neutralizing activity in breast milk samples (among those infants who were rotavirus IgA negative at age 6 weeks and completed the study ATP) will be examined. The independent effect of the level of breast milk neutralizing activity on the rate of rotavirus IgA seroconversion at age 18 weeks will be assessed using logistic regression. Breast milk arm (immediate vs. withholding) and level of rotavirus neutralizing antibody in 6-week serum sample will be included as independent variables and effect modification will be examined. Analyses will also be performed using rotavirus IgA seroconversion rate at age 14 weeks as the endpoint. Exploratory analyses will be performed for correlation between level of breast milk neutralizing activity (in breast milk samples at ages, 6, 10 and 14 weeks) and rotavirus IgA level at ages 14 and 18 weeks in the different two arms.

- 1. . **Enrollment Time Period**

Refer to section 5

- 1. **Inclusion Criteria :**

Same as section 3.4

AND

- Mother reports she intends to breastfeed her infant through at least age 14 weeks (Exclusive or non exclusive breast feeding).
  1. **Exclusion Criteria**

Refer to section 3.5

AND

- Biological mother not available for participation in the study.
  1. **Elimination Criteria During the Study**

Refer to section 3.6

- 1. **Contraindication of the Vaccine**

Refer to section 3.7

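### Study B uses withheld breastfeeding to keep milk out of the oral-fluid sample, but sets no feeding condition at 18 weeks, the only oral-fluid sample after dose 3

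*Protocol*

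**What the plan says.** The Study Design section of Study B defines the arms. For the first: "In arm 1, mothers would be asked to breast feed immediately before administration of the Rotarix dose". For the second: "In arm 2, mothers would be asked to withhold breast feeding for one hour before and one hour after each Rotarix®dose". The schema uses the same numbering.

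The same section takes OF from the withholding arm at 6, 14 and 18 weeks. It justifies the choice of arm by the absence of breast-milk contamination: "Arm 1 provides an ideal setting to assess the value of non-invasive OF assays for rotavirus immune response".

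In the schema, the withholding arm's 14-week visit includes "One hour withholding of breast feed before and after vaccination", and the 6-week visit carries the same line. The 18-week visit has a single entry: "Blood and oral fluid samples obtained from infant".

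Study B's Analysis of immunogenicity compares OF with serum in two ways. The first is "by the concordance in detecting seroconversion, as defined above, at 14 and 18 weeks". The second is the correlation of titres at 6, 14 and 18 weeks, reported as R-squared, for which the protocol says that no cutoff is used.

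**The concern.** Breast milk contains rotavirus IgA; Study B itself assays milk for it. OF taken soon after a feed may therefore carry maternal IgA, which the assay would count as the infant's. The protocol recognises this and relies on withholding to prevent it. That protection stops when dosing stops, so it is absent at 18 weeks.

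The 18-week sample matters. It is the only OF sample that can reflect all three doses, it coincides with Study B's primary serum endpoint, and it enters both the concordance and the correlation. The protocol collects nothing at that visit that would allow a later correction: no time of last feed is called for, and milk is sampled only at the vaccine visits. What is at stake is Secondary Aim II's question of how well oral IgA tracks serum IgA.

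**Working it through.** **1. Feeding condition at each OF sample (withholding arm)**

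| Visit | Rotarix dose | OF sample | Feeding condition | Milk sample |
|---|---|---|---|---|
| 6 weeks | 1st | yes, before vaccine | withheld one hour before and after dose | yes |
| 10 weeks | 2nd | no | withheld one hour before and after dose | yes |
| 14 weeks | 3rd | yes | withheld one hour before and after dose | yes |
| 18 weeks | none | yes | none stated | no |

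At the vaccine visits mothers are collected about an hour before the expected immunization time and told not to feed, and the infant is bled before vaccination. A sample taken with that blood falls inside the no-feed window. At 18 weeks there is no immunization to start such a window. Eligibility asks only for an intention to breastfeed through at least 14 weeks, so at 18 weeks some infants may be breastfed and others weaned. Any contamination would then differ between infants.

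**2. The section's own figure (context only)**

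Inputs from Sample Size consideration: 45% v 62.5%, power 0.85, two-sided alpha 0.05, 20% drop-out, 5% seropositive at 6 weeks. The pooled chi-square formula without continuity correction gives 145 evaluable per group. Then 145 / (0.80 × 0.95) = 145 / 0.76 = 190.8, or 191, which is the stated figure. This point does not touch it.

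**3. Possible size for the concordance analysis**

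- Evaluable infants from the 200 enrolled: 200 × 0.80 × 0.95 = 152.
- Expected serum-negative at 18 weeks: 1 − 0.625 = 0.375, or 152 × 0.375 = 57 infants.
- Let c be the share of serum-negative infants made OF-positive by milk. The protocol gives no value, so c is assumed. If all of these infants would otherwise have been OF-negative, added discordance = 0.375 × c.

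| Assumed c | Added discordance | Infants (of 57) |
|---|---|---|
| 5% | 1.9 points | about 3 |
| 20% | 7.5 points | about 11 |
| 40% | 15.0 points | about 23 |

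**4. Direction**

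Milk IgA can also turn a serum-positive, OF-negative infant OF-positive, which adds apparent agreement. Let the uncontaminated OF test have sensitivity Se and specificity Sp, and let c be the same in both groups. Then:

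net loss of concordance = c × [0.375 × Sp − 0.625 × (1 − Se)]

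With Sp = 1 this is zero at Se = 1 − 0.375 / 0.625 = 0.40. Above that value contamination lowers concordance; below it contamination raises it. The protocol gives neither Se nor Sp, so the sign cannot be settled. On either side of that value the 18-week concordance partly reflects recent feeding.

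**The case against.** The best reply on the main point is that the protocol is silent and does not permit a feed before the 18-week sample. Collection detail may sit in the standard operating procedures listed in the time line. The 14-week sample, taken after two doses, is protected and enters both analyses. The aim is secondary and carries no sample size of its own. All of this stands, and it limits the weight of the point. It does not close the gap: the protocol spells out the feeding condition at every other OF visit and makes it the reason for choosing the arm.

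Three stronger readings are tempting, and the document does not support them.

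- **OF will be collected from the wrong arm and every sample contaminated.** The sentence before the mislabelled one names the withholding arm, the schema lists OF only there, and the Lab Assay table restricts it to the withholding group at all three ages. Even in the immediate arm, mothers are told not to feed from pick-up, and blood is drawn before the observed feed, so universal contamination would not follow.
- **The serum cutoff is imposed on OF and makes the substudy uninterpretable.** The 20 U/ml rule reaches the concordance only through a back-reference. This may mean the serum reference alone, with OF positivity left open. The correlation uses no cutoff, and the protocol describes it as the best indication of how well OF represents serum. The wording is ambiguous, and only for concordance.
- **Concordance will fall by a known amount.** Every size given above rests on an assumed c, and the direction is open.

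**Conclusion.** The point holds for the 18-week sample. The protection that justifies OF sampling in the withholding arm is tied to doses, and the only OF sample after dose 3 has no stated feeding condition and no recorded feed time. It affects one of two concordance time points and one of three correlation time points, for all infants sampled in that arm.

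The possible added discordance is about 2 to 15 points for c between 5% and 40%. This rests on the protocol's planning rate of 62.5%, the assumed c, and the affected infants being otherwise OF-negative. Contamination of serum-positive infants could offset or reverse it. The Study B primary comparison and its sample size are unaffected. The arm label and the cutoff wording are minor corrections in the same text. This is a cheap improvement to a secondary aim and not a threat to the trial's main conclusion.

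**What to change.** 1. At 18 weeks, collect OF after the same pre-sample no-feed interval as at 6 and 14 weeks. Alternatively, record time since last breastfeed at that visit and restrict or stratify the concordance and correlation by it. Transport to the visit is already provided, so the cost is one instruction or one data item, plus a short feed delay or some excluded samples. It must be in place before collection, because an unrecorded feed time cannot be recovered.
2. In Study Design, change the arm label in the OF rationale to the withholding arm (Arm 2). This costs one word and changes no procedure.
3. In Analysis of immunogenicity, state that the 20 U/ml seroconversion rule is the serum reference, and give OF positivity its own threshold. That threshold should not be chosen and evaluated on the same pairs without validation, because the agreement would then look better than it is. Otherwise, rely on the cutoff-free correlation. The cost is wording, plus validation if a threshold is derived from the trial's own samples.
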